#### Isokinetic dynamometry

The Biodex System 3 Pro isokinetic dynamometer (Biodex Medical System System 4, Biodex Medical Systems, Inc., Shirley, NY, USA) will be used for the eccentric fatigue protocol and MVIC of the quadriceps muscle bilaterally (alternating sides). This device is considered reliable and reproducible for muscle evaluations
[44] and has been used on patients with different diseases such as heart failure
[45], osteoarthritis
[46] and spinal cord injury
[47], as well as on different populations ranging from children
[46] to the elderly
[47-49]. In the proposed study, peak torque (maximum generation of force by the muscle) and the Muscle Fatigue Index
[50,51] will be analyzed.

The volunteer will first perform three 60-second sets of active stretching of the quadriceps muscle bilaterally, followed by warm up consisting of pedaling a stationary bike (Inbramed®, Inbramed, Porto Alegre, RS, Brazil) at 100 rpm for 5 minutes without load. The volunteer will then be positioned on the isokinetic dynamometer (previously calibrated following the instructions in the manual), duly aligned and stabilized by straps to avoid compensatory movements. The rotation axis of the dynamometer will be aligned with the movement axis of the knee being evaluated at the level of the lateral epicondyle of the femur. Chair height and base, distance of the support, accessory level and base of the dynamometer will be adjusted to the needs of each individual. During the test, the volunteer will be instructed to cross his/her arms over the chest and the axis of the dynamometer will be positioned parallel to the center of the knee.

MVIC will consist of three 5-second isometric contractions of the knee extensors (Figure 
1). The greatest torque of the three contractions (peak torque) will be used in the statistical analysis. This variable was chosen based on the fact that it reflects the maximum generation of force by the muscle
[52]. The instructions will be given first and the volunteers will receive verbal encouragement during the MVIC.

**Figure 1 F1:**
[figure not shown]
Realization of isokinetic dynamometry maximum voluntary isometric contraction (MVIC) of the quadriceps muscle.

The volunteers will perform the isokinetic eccentric fatigue protocol for the quadriceps muscle bilaterally (Figure 
2), which will consist of 75 isokinetic eccentric contractions of the knee extensors (5 sets of 15 repetitions with a 30-second rest period between sets) at a velocity of 60°.sec^-1^ in both the eccentric and concentric phases, with a 60° range of motion (between 90° and 30° of knee flexion) for each leg. At each contraction, the dynamometer will automatically (passively) position the knee at 30° and will then flex the knee until reaching 90°. The volunteers will be instructed to resist the knee flexion imposed by the dynamometer with maximum force. The instructions will be given first and the volunteers will receive verbal encouragement throughout the exercise. This protocol has proven to be efficient and reliable for exercise-induced muscle damage
[19].

**Figure 2 F2:**
[figure not shown]
Realization of the isokinetic eccentric fatigue protocol for the quadriceps muscle.

The order on both the MVIC and isokinetic eccentric fatigue protocol for the quadriceps muscles will be determined randomly by lots using sealed, opaque envelopes.

#### Low-level laser therapy protocol

A five-diode cluster laser device (810 nm and 200 mW for each diode) (THOR Photomedicine®, Thor Photomedicine, Chesham, UK) will be used for LLLT. For the placebo group, a laser device that produces the same characteristics (cluster) will be used, but will not emit Joules. The LLLT protocol will be performed with the cluster in direct contact with the skin at six different sites over the quadriceps muscle (2 medial, 2 lateral and 2 central), totaling 30 points on each leg. The volunteers will be distributed in the following groups:

– Group A – 4 Joules per point (irradiation time: 20 seconds), 120 Joules of total energy irradiated over the muscle with 120 seconds of total irradiation time.

– Group B – 6 Joules per point (irradiation time: 30 seconds), 180 Joules of total energy irradiated over the muscle with 180 seconds of total irradiation time.

– Group C – 8 Joules per point (irradiation time: 40 seconds), 240 Joules of total energy irradiated over the muscle with 240 seconds of total irradiation time.

– Group D – 0 Joules per point (“irradiation” time: 40 seconds), 0 Joules of total energy irradiated over the muscle with 240 seconds of total “irradiation” time.

The order of the LLLT protocol on the quadriceps muscles will be determined randomly by lots using sealed, opaque envelopes.

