### Blinding

The participants will be blinded to the allocation to the different groups. One researcher will be in charge of the randomization process and will program the laser device based on the results of the randomization. A second researcher will perform the LLLT and will be blinded to the doses and respective groups. These researchers will not participate in any of the evaluation phases, which will be performed by a third researcher blinded to the allocation of the subjects to the different groups. When blood collection is involved, the evaluations will be performed by an experienced, trained nurse, who will only participate in these evaluations. The statistician will be blinded to the group allocation until completion of the statistical analyses.

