All questionnaires will be administered in a reserved room and are to be filled out completely. If an individual refuses or is unable to cooperate, Examiner 2 will mark “NR” (no record) in capital letters on the exam. To avoid hurried responses from the participants, no time constraints will be applied.

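### Group-specific irradiation times contradict the claim that the laser operator is blinded to dose: Groups A and B are identifiable as active, and phase 2 may separate active from placebo

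*Protocol article*

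**What the plan says.** The Blinding section of the protocol article makes an explicit claim about the operator: "A second researcher will perform the LLLT and will be blinded to the doses and respective groups". A different researcher randomises and programs the laser. Neither of these two takes part in evaluations, which fall to a third, blinded researcher. A nurse is involved only where blood is taken, and the statistician is blinded until the analyses are complete. Participants are also said to be blinded.

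The section Low-level laser therapy protocol describes a five-diode cluster at 200 mW per diode, held against the skin at six sites per leg, and fixes the times by group. The entry for Group A reads "4 Joules per point (irradiation time: 20 seconds"), which the article sums to 120 J and 120 s for the muscle. Group B has 6 J and 30 s at each site, summing to 180 J and 180 s. For Group C the text has "8 Joules per point (irradiation time: 40 seconds"), with sums of 240 J and 240 s. Placebo Group D copies the timing of C (40 s per site, 240 s overall) at 0 J.

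On the placebo equipment it says that "a laser device that produces the same characteristics (cluster) will be used, but will not emit Joules".

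Under Treatment phase 2, Groups A, B and C all move to whichever protocol performed best in phase 1. Group D continues on placebo. There are three sessions a week for 4 weeks, 12 in total. No sham duration is given for this phase.

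**The concern.** The person holding the probe experiences the application time directly, at 6 sites on each of 2 legs, which is 12 applications per participant. Programming by someone else hides the setting but not how long each application lasts. With three different durations and no masking described, the operator cannot be blinded to dose in the way the article claims.

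This matters because the primary outcome is peak torque from a maximal voluntary contraction, which depends on effort. The questionnaires and the fatigue scale are self-reported. For such measures the participant is part of the measuring instrument, so a blinded evaluator does not fully protect against expectation picked up from an operator who knows that the treatment is active. Phase 1 performance also selects the phase 2 protocol, so a bias in phase 1 could carry forward.

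**Working it through.** **Inputs**, all from Low-level laser therapy protocol: 0.2 W per diode; 5 diodes at 6 sites = 30 points per leg; 20, 30, 40 and 40 seconds per site for A, B, C and D.

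**Step 1: reproduce the plan's figures.** Energy per point = 0.2 W × seconds for the active groups. Total energy per leg = energy per point × 30. Total time per leg = 6 × seconds.

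| Group | Seconds per site | J per point | J per leg | Seconds per leg | Both legs |
|---|---|---|---|---|---|
| A | 20 | 0.2 × 20 = 4 | 4 × 30 = 120 | 6 × 20 = 120 | 4 min |
| B | 30 | 0.2 × 30 = 6 | 6 × 30 = 180 | 6 × 30 = 180 | 6 min |
| C | 40 | 0.2 × 40 = 8 | 8 × 30 = 240 | 6 × 40 = 240 | 8 min |
| D | 40 | 0 (sham) | 0 | 6 × 40 = 240 | 8 min |

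Every stated figure is reproduced. The times and energies are consistent with each other, and at fixed power the time determines the dose.

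**Step 2: what time reveals in phase 1.** 20 seconds occurs only in A, 30 seconds only in B, and 40 seconds in C or D. The only sham lasts 40 seconds, so a shorter application also means active treatment.

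The article does not state the allocation ratio; assume 1:1:1:1. An operator who uses time alone and guesses between C and D is right with probability 0.25 × 1 + 0.25 × 1 + 0.25 × 0.5 + 0.25 × 0.5 = 0.75, against 0.25 by chance.

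Half of all participants (A and B), or two thirds of the active ones, are known to be active with certainty. At 40 seconds the probability of placebo is 0.25 / (0.25 + 0.25) = 0.5, up from 0.25 without the time cue. The 8 J versus placebo contrast itself is not broken by time.

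**Step 3: what time reveals in phase 2.** Assume that the sham stays at 40 seconds, the only sham time the article states.

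| Protocol selected | Active time | Sham time | Active versus placebo by time | Active groups whose time changes |
|---|---|---|---|---|
| 4 J | 20 s | 40 s | separated for everyone | B and C |
| 6 J | 30 s | 40 s | separated for everyone | A and C |
| 8 J | 40 s | 40 s | not separated | A and B |

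For two of the three possible selections, time would separate active from placebo at all 12 sessions. Whichever protocol is selected, two of the three active groups change duration between phases while D, on this assumption, does not.

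**The case against.** The strongest reply is that the trial's blinding rests on several people and this point touches only some of them. The evaluator, the nurse and the statistician are kept apart from treatment delivery, and duration tells them nothing. The operator attends no evaluation, so the verbal encouragement during testing does not come from that person. CK and LDH, the two declared secondary outcomes, are laboratory measurements. All of this stands. It limits the route for bias to cues passed during treatment and to what participants notice themselves. It does not make the statement about the operator true.

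Several stronger readings are tempting, and the article does not support them:

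- *That blinding as a whole fails.* It does not, for the reasons just given.
- *That time reveals every group.* The sham was matched to Group C at 40 seconds, so time does not tell those two apart in phase 1.
- *That the placebo device gives Group D away.* The article says it has the same cluster characteristics and says nothing about a difference in look or handling. A statement that the units are indistinguishable would be useful, but recognisability cannot be inferred.
- *That participants are unblinded in phase 1.* Each has one session at one duration, with nothing to compare it with, and nothing says they are told the group timings. The cue is plausible mainly in phase 2, where a participant may notice a change and would still have to interpret it.
- *That phase 2 certainly separates the arms.* This needs both an unchanged sham time and selection of the 20 or 30 second protocol. The article is silent on the sham time, and a fuller protocol may settle it.
- *That the operator also handles questionnaires.* The Questionnaires section says "If an individual refuses or is unable to cooperate, Examiner 2 will mark" a missing record, but equating that label with the second researcher of the Blinding section is a guess. It is a labelling point to clarify.

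**Conclusion.** The point holds in a limited form. The Blinding section and the laser section contradict each other on operator blinding to dose: as written, Groups A and B are identifiable by time and known to be active.

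Under equal allocation, time alone gives 75% correct group identification against 25% by chance. This assumes that the time the operator perceives equals the stated irradiation time and that the operator knows, or works out, which time belongs to which group.

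In phase 2, complete separation of active from placebo is a conditional risk. It arises if the 4 J or 6 J protocol is selected and the sham stays at 40 seconds. The change of duration for two of the three active groups arises whichever protocol is selected, unless durations are masked.

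The size of any resulting bias in peak torque cannot be derived from the article. The point should still be settled because the outcome depends on effort and because blinding that has been lost cannot be restored in the analysis.

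**What to change.** Reconcile the sections Blinding, Treatment phase 2 and Low-level laser therapy protocol as follows:

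1. Use one apparent application time for all four groups, with the end of emission masked from operator and participant. Each group's stated energy and emission time stay as they are, so no dose changes.
2. In phase 2, match the sham's apparent time to that of the active protocol. Keeping the phase 1 apparent time would also remove the change of duration between phases.
3. State whether the active and placebo units are indistinguishable to the operator, and clarify who Examiner 2 is.
4. If the device cannot mask the end of emission, withdraw the claim that the operator is blinded to dose and report this as a limitation. The article does not say whether the device can do this.

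Cost: if the common apparent time is the 40 seconds already used for C and D, the added contact time per leg is 6 × (40 − 20) = 120 seconds in Group A and 6 × (40 − 30) = 60 seconds in Group B, so at most 2 minutes. The rest is device programming and an amendment. The Trial status section says that recruitment is under way, so any participants already treated under the current timings should be noted and identified when the results are reported.

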#### Data analysis

Peak torque determined by the isokinetic dynamometer will be the primary outcome and CK and LDH activity determined from the blood samples will be the secondary outcomes. The Shapiro-Wilk test will be used to test the data with regard to Gaussian distribution. Data will be expressed as mean and standard deviation values. Two-way repeated-measures analysis of variance with the *post hoc* Bonferroni test will be used for inter-group and intra-group comparisons. The level of significance will be set to 5% (*P* < 0.05) for all comparisons. Statistical analysis will be performed using the SPSS program, version 13.0 (Chicago, IL, USA).

## Discussion

The purpose of this randomized clinical trial is to evaluate the efficacy of pre-exercise LLLT on the performance of the quadriceps muscle (peak torque, total muscle work, maximum power and fatigue index – normalized by body mass) in individuals with DM-2. The study will support the practice of evidence-based to the use of LLLT in improving muscle performance in Individuals with DM-2. Data will be published after the study is completed.

## Trial status

Patient recruitment is currently underway.

## Abbreviations

CK: creatine kinase; DM: diabetes mellitus; DM-2: type 2 diabetes mellitus; DQOL: Diabetes Quality of Life; FRT: functional reach test; LDH: lactate dehydrogenase; LEFS: Lower Extremity Functional Scale; LLLT: low-level laser therapy; MVIC: maximum voluntary isometric contraction; NR: no record; PAID: Problem Areas in Diabetes; PSFS: Patient Specific Functional Scale; TUGT: timed up-and-go test; VAS-F: visual analog scale for fatigue.
